### Participant timeline

Baseline assessment (at time 0-T0) will be completed before the interventions are administered. Participants will undertake tDCS treatments (active or sham) plus a TAU for six weeks delivered for three times a week (18 session). Participants will be evaluated at the end of the treatment (at time 1-T1) and one-month later (at time 2-T2), three months later (at time 3-T3), six months later (at time 4-T4) and one year later (at time 5-T5). In the last follow-up, participants will be asked to indicate whether they believe they were receiving active or sham tDCS.

See Fig. 1 for details on the specific assessment of each visit.

**Fig. 1 Fig1:**
[figure not shown]
Study procedure and assessments. *AU* as usual, *tDCS* transcranial direct current stimulation, *BMI* Body Mass Index

### Sample size

The sample size was calculated by a priori analysis in G * Power, version 3.1.9.7 (The G*Power Team, Düsseldorf, Germany).

Assuming a correlation of 0.80 in the primary outcome measure (EDRC score of EDI-3 questionnaire) with an estimated f = 0.08, α value = 0.05 (i.e., probability of false positives of 5%), and β = 0.80 (i.e., at least 80% power), the sample size that was required for repeated-measures analysis of variance (ANOVA) with 2 groups (active tDCS vs sham tDCS) and 6 measurements (T0 vs. T1 vs. T2 vs. T3 vs. T4 vs. T5) was 68 (i.e., 34 per group). Considering a 15% dropout rate in the follow-ups, we will plan to recruit a total of 80 participants (i.e., 40 per group).

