### Outcomes measures

#### Primary outcome measure

We believe that active tDCS, coupled with TAU, will enhance outcome of traditional treatment and will have a substantial impact on symptoms recovery of AN.

The primary end-point of the study is significant improvement on AN psychopathology at T1, assessed as changes in EDI-3 ED-specific (EDRC score).

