### Statistical methods

The Shapiro–Wilk test will be used to test the normality of the data and Levene’s test for the homogeneity of variances. When data will be normally distributed and the assumption of homogeneity will be not violated, parametric analyses will be computed. When one assumption will be not meet, non-parametric tests will be conducted or a log-transformation of distribution will be applied, if appropriate.

The groups will be compared on demographic and categorical variables using Chi-Square analyses. The primary outcome (EDRC score of EDI-3) will be included in a General Linear Model and will be analyzed by means of repeated measures ANOVA with Group (active tDCS + TAU vs sham tDCS + TAU) as between-factor and Follow-ups (T0-T1 vs T0-T2 vs T0-T3 vs T0-T4 vs T0-T5) as within-factor. The same analyses will be applied to the secondary psychological outcomes (EAT-26 total score, BUT-GSI, and CBCL 6–18, YSR 11–18, MASC-2 and CDI-2 subscale’s t-scores). Post hoc comparisons will be run by means of Bonferroni test.

For secondary neurophysiological outcomes, the differences between the left and right hemisphere at baseline and between the recordings T0 and T1 will be evaluated on both TEPs component and frequency through a non-parametric cluster based permutation tests to correct for multiple comparisons as developed in the ft_timelockstatistics\ ft_freqstatistics functions in Fieldtrip [74]. The EEG signal will be analyzed for defining a resting state pattern with frequency inspection, using a Fourier analysis. For TMS data, prior to undergoing ANOVA, the normal distribution of data will be assessed by means of the Shapiro-Wilks test. The level of significance was set at 0.05. For the SICI, SAI, and iTBS protocols, we will perform three ANOVAs on the normalized values calculated as the percentage of the mean peak-to-peak amplitude size of the unconditioned TS with GROUP (active vs sham) as the between-subject factor and ISI (for SICI and SAI protocols) or TIME (for iTBS protocol) as within-subject factors. When a significant main effect will be reached, Bonferroni post hoc comparisons will be performed to characterize the specific effect.

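### The stated 80% power with 68 participants is not the power of the planned EDRC analysis or of the T1 primary end-point

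*Protocol article*

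**What the plan says.** Three sections of the protocol article bear on this.

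- **Primary outcome measure:** "The primary end-point of the study is significant improvement on AN psychopathology at T1", measured as change in the EDRC score of the EDI-3. This is one time point, the end of treatment.
- **Sample size:** repeated EDRC scores are taken to correlate at 0.80. The effect size enters "with an estimated f = 0.08", the false-positive rate is 5%, and the power target is written as "β = 0.80 (i.e., at least 80% power"). These inputs are applied to a "repeated-measures analysis of variance (ANOVA) with 2 groups (active tDCS vs sham tDCS) and 6 measurements", T0 to T5. The resulting total of 68, or 34 in each arm, is raised to 80 for 15% dropout in the follow-ups. The section does not say whether the effect tested is Time or Group by Time.
- **Statistical methods:** EDRC enters a repeated-measures ANOVA that compares the two arms. Its other term is given as "Follow-ups (T0-T1 vs T0-T2 vs T0-T3 vs T0-T4 vs T0-T5) as within-factor", and Bonferroni post hoc comparisons follow. No T1 comparison is singled out. An ANOVA over six raw time points is written for BMI, a secondary outcome, but not for EDRC.

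**The concern.** The test that was sized, the test that is planned and the end-point are three different things. A power figure belongs to one test, one effect and one set of assumptions. If the test sized is not the one that decides the trial, the 80% tells the reader nothing definite about the chance of detecting a benefit at T1.

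The article gives no T1 difference, in SD units or in EDRC points, from which that chance could be worked out. At stake is the justification of the sample size for the primary end-point, which here rests on a figure belonging to another test.

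**Working it through.** **Inputs.** From the Sample size section: f = 0.08, correlation ρ = 0.80, α = 0.05, two groups, m = 6 measurements, N = 68. Assumed, because not stated: full sphericity, equal correlation between all pairs of visits, and a raw EDRC SD of 1 at each visit.

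**1. Reproducing 68.** The G*Power within-type test has λ = f²·N·m/(1−ρ), with df1 = m−1 and df2 = (N−2)(m−1).
- N = 68: λ = 0.0064 × 68 × 6/0.2 = 13.06 on 5 and 330 df; power 80.04%.
- N = 67: power 79.3%.
- Dropout: 68/0.85 = 80.

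Both stated numbers are arithmetically right. Other readings do not give 68:
- Five levels at the same f and ρ: λ = 0.0064 × 68 × 5/0.2 = 10.88 on 4 and 264 df; power 74.8%.
- Between-group effect over six measurements: λ = 0.0064 × 68 × 6/(1 + 5 × 0.8) = 0.52 on 1 and 66 df; power 11%.

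With two groups, the Time main effect has the same λ and df as the Group by Time interaction, so 68 fits either.

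**2. What the planned analysis does with that hypothesis.** Take the interaction reading, which is the one that compares treatments. Five changes from T0 carry the same information as the 5-df interaction, but the planned ANOVA splits it into a 1-df Group effect and a 4-df Group by Follow-ups interaction. To see the split, scale each assumed pattern of group differences over T0 to T5 so that f = 0.08. This requires the SD of the six differences (divisor 6) to be 2 × 0.08 = 0.16.

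- Group effect: the variance of a participant's mean change is (1−ρ)(1 + 1/5) = 0.24.
- Interaction: λ = (68/4)·Σ(deviation of each change difference from their mean)²/(1−ρ).

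| Assumed pattern | Group effect, 1 df | Interaction, 4 df |
|---|---|---|
| Constant from T1 | 94.5% | 5% |
| T1 only | 11% | 81% |
| Linear by visit number | 64.5% | 56% |

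All three patterns have 80% power in the 5-df test. The planned tests share out that power differently each time.

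**3. Power at T1.** The SD of the T0-T1 change is √(2(1−ρ)) = √0.4 = 0.632.
- **Constant from T1, or T1 only:** the pattern (0,1,1,1,1,1) or (0,1,0,0,0,0) has SD 0.3727, so the T1 difference is 0.16/0.3727 = 0.43 SD. Standardised on the change, this is 0.429/0.632 = 0.68. Power at two-sided 0.05 is 79% with 34 per arm and 85% with 40 per arm.
- **Linear by visit number:** the pattern (0,1,2,3,4,5) has SD 1.708, so the T1 difference is 0.16/1.708 = 0.094 SD, or 0.148 on the change. Power is 9% with 34 per arm.
- **If T1 is one of five Bonferroni comparisons** (family size assumed, α = 0.01): the 79% becomes 56%.

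**4. What 34 per arm can detect at T1.** Under the noncentral t, 80% power at two-sided 0.05 needs a standardised difference of 0.69. Multiply by the residual SD of the analysis chosen:

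| T0-T1 correlation | Baseline-adjusted ANCOVA, √(1−ρ²) | Unadjusted change, √(2(1−ρ)) |
|---|---|---|
| 0.8 | 0.69 × 0.600 = 0.41 SD | 0.69 × 0.632 = 0.44 SD |
| 0.5 | 0.69 × 0.866 = 0.60 SD | 0.69 × 1.000 = 0.69 SD |

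The correlation of 0.5 is an assumption, chosen to show a less favourable case.

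**The case against.** Several objections have force.

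- **The arithmetic is right.** Both 68 and 80 reproduce. The fault is one of alignment, not of calculation.
- **The interaction is inferred.** The article names neither the effect nor its degrees of freedom, and the Time main effect also gives 68. This stands as a limit on what can be attributed to the plan. It does not rescue the figure, since a Time main effect is not a treatment comparison.
- **The planned analysis uses the same information and can do better.** Under a constant effect its Group term has 94.5% power. True, but under a T1-only effect the same term has 11%. The stated 80% describes neither.
- **A reader might infer that the trial is underpowered.** The documents do not support that. Under a sustained or T1-only effect, T1 power is 79% with 34 per arm and 85% with 40. The 15% dropout is placed in the follow-ups, so more than 34 per arm may be assessed at T1. The 9% comes from a build-up pattern that the documents do not suggest.
- **A reader might also take 9% and 79% as bounds.** They are examples; an effect that appears only from T3 would give 5%.
- **A reader might doubt the 0.80 correlation or sphericity.** Nothing in the article contradicts either.
- **The β label is a slip.** Taken literally, β = 0.80 means 20% power, but the accompanying parenthesis makes the intention clear.

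The mismatch between the three sections survives all of these.

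**Conclusion.** The point holds as a mismatch. The 80% at N = 68 is the power of a 5-df test over six raw EDRC measurements. The plan analyses EDRC as five changes from T0 and places its primary end-point at T1, so the figure applies to neither.

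T1 power is undetermined from the stated inputs, because the same f of 0.08 is compatible with a T1 difference of 0.43 SD or 0.09 SD, depending on how the effect is spread over visits. These illustrations rest on correlation 0.80 between all visits, equal SDs, two-sided 0.05 and unadjusted T1 changes. The identification of the sized test rests on its being the setting that returns 68. The conclusion is that no power is stated for the primary end-point, not that 80 participants are too few.

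**What to change.** Keep 80 recruited and change the text in two places.

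1. **Statistical methods:** name one primary test, the between-arm EDRC contrast at T1, at two-sided 0.05 and outside the Bonferroni post hoc family. Adjustment for T0 EDRC is preferable; that score is already collected.
2. **Sample size:** restate power for that same test. With 34 evaluable per arm there is 80% power for about 0.41 SD (T0-T1 correlation 0.8) to 0.60 SD (correlation 0.5) if the baseline-adjusted ANCOVA is adopted, or about 0.44 to 0.69 SD if unadjusted changes are kept. The figures must match the test named in step 1, because the ANCOVA values do not hold for change scores. Give the difference in EDRC points as well. Label the six-visit calculation as support for the longitudinal secondary analysis, and write 1−β = 0.80.

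The cost is wording only, with no extra participants or visits. The drawback is that the stated figure may become less favourable, particularly if the T0-T1 correlation is below 0.80.

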### Allocation

Before the stratified randomization, screening for clinical eligibility will be completed by a trained experimenter.

Stratified randomization will be performed via the minimal sufficient balancing method to prevent disparities at baseline. Namely, age, BMI and AN severity assessed by the EDI-3, will be taken in to account. Participants will be randomly assigned to two treatment groups: 1. TAU plus active tDCS (experimental treatment); 2. TAU plus sham tDCS (control treatment).

The stratified randomization will be carried out by an independent researcher.

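### The primary model leaves out the variables used to balance allocation and fixes the baseline EDRC slope at 1, so the analysis is conservative and less precise than it could be

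*Protocol article*

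**What the plan says.** The Allocation section of the protocol article states: "Stratified randomization will be performed via the minimal sufficient balancing method to prevent disparities at baseline". It names three variables: "Namely, age, BMI and AN severity assessed by the EDI-3, will be taken in to account". It does not say which EDI-3 score stands for severity.

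The section Primary outcome measure defines the endpoint as change in EDRC at T1. The Statistical methods section gives the analysis: "The primary outcome (EDRC score of EDI-3) will be included in a General Linear Model". The only between-subject term is treatment group, and the within-subject term is the set of five changes from T0: "Follow-ups (T0-T1 vs T0-T2 vs T0-T3 vs T0-T4 vs T0-T5) as within-factor". No covariate is listed there, and no other section adds one. The same analysis is prescribed for the secondary psychological outcomes. BMI gets a repeated-measures ANOVA in which T0 is one level of time.

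The Sample size section supplies the one planning figure that bears on baseline adjustment: "Assuming a correlation of 0.80 in the primary outcome measure".

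**The concern.** Two features of the design and analysis do not fit together.

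First, minimal sufficient balancing makes the arms more alike on the chosen variables than simple randomisation would. If those variables predict outcome, part of their variance has been removed from the treatment comparison by design. A model that omits them still counts that variance as error, so its standard error is larger than the true sampling error.

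Second, a change score assumes that each unit of baseline EDRC carries over fully to follow-up. With equal variances at the two visits, the slope that minimises variance is the baseline-to-follow-up correlation, not 1.

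What is at stake is power. The trial plans 80 participants and 68 completers, sized at 80% power with nothing to spare, and it is giving up precision that its own baseline data would supply.

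**Working it through.** **Inputs from the article.** Correlation 0.80, f = 0.08, alpha 0.05, 80% power, 2 groups, 6 measurements, 68 completers (34 per group), 15% dropout, 80 recruited (Sample size). Balancing variables (Allocation). Model terms (Statistical methods).

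**Assumptions not in the article.** Sphericity in the sample-size check; equal EDRC variance at T0 and T1; 0.80 read as the T0–T1 correlation; a T1 difference of 0.43 SD; the alternative correlation of 0.5.

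**1. The plan's own figure.** For the within-between interaction, λ = f²·N·m/(1−ρ) = 0.0064 × 68 × 6/0.20 = 13.06, with 5 and (68−2) × 5 = 330 degrees of freedom. Power is 0.800, so 68 reproduces, and 68/0.85 = 80. The sample size is not in dispute.

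**2. Variance of the T1 comparison, in units of SD².**
- Change score: 2(1−ρ) = 2 × 0.20 = 0.40
- Baseline-adjusted: 1−ρ² = 1 − 0.64 = 0.36
- Ratio: (1+ρ)/2 = 0.90; standard-error ratio √0.90 = 0.949

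At the adjusted variance, 68 × 0.90 ≈ 61 completers would give the precision that 68 give with change scores.

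**3. Power at 34 per arm.** The difference detectable at 80% power by change scores (normal approximation) is (1.96 + 0.84) × √(0.40 × 2/34) = 0.43 SD. Adjusted, it is (1.96 + 0.84) × √(0.36 × 2/34) = 0.41 SD. Two-sided noncentral-t power at 0.43 SD:

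| Correlation | Variance ratio | Change score | Adjusted |
|---|---|---|---|
| 0.80 (article) | 0.90 | 79% | 83% |
| 0.50 (assumption) | 0.75 | 42% | 52% |

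The degrees of freedom spent on three covariates do not change these figures to the nearest percent.

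**4. Size of the unadjusted test.** Suppose the balanced EDI-3 score is EDRC and balance is perfect. The difference in mean change then varies with variance proportional to 0.36, while the model estimates 0.40. The true size is 2[1 − Φ(1.96/√0.90)] = 2[1 − Φ(2.066)] = 3.9%. The same formula at an assumed correlation of 0.5 gives 2.4%. Perfect balance makes these limits, not expected values.

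**5. Simulation with imperfect balance.** Allocation of 80 participants was simulated 2,500 times with tuning values that the article does not give: imbalance flagged at |t| > 1.04, biased coin 0.70, normal data, EDRC as the severity score. With ρ = 0.80 and no age or BMI effect, the unadjusted change-score test had type I error of about 3.9%. It was 3.0–3.2% with ρ = 0.5, or with age and BMI each given an assumed coefficient of 0.2 for T1 EDRC. Its standard error was about 4–11% too large. The adjusted model gave 4.4–4.8%. Monte Carlo error is about √(0.05 × 0.95/2500) = 0.4 points.

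**The case against.** **This may be settled in an analysis plan that is not shown.** A covariate list is often left to one. But the article does more than name a method: it lists the between-factor and the within-factor. That is a stated model, and it does not match the stated allocation. The objection weakens the point without removing it.

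**The plan does use baseline.** This stands. Subtracting T0 is a form of adjustment for baseline EDRC, with the slope fixed. A reader might infer that all the balancing variables are ignored; that is right for age and BMI only. If the severity score is not EDRC, it too is left out.

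**The p-values might be thought invalid.** A reader might infer a threat to validity from a standard error that does not match the allocation. The documents do not support that: the standard error is too large, not too small, the estimate is unbiased, and type I error falls below 5%.

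**The gain is small at the plan's own correlation.** This also stands: about four points of power at T1. Larger gains need a lower correlation, or age and BMI effects, and the article gives neither.

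**The figures describe one visit, not the five-change model.** True, although the endpoint is at T1. For the Group main effect over five changes, with all correlations 0.80 and a constant 0.43 SD effect (assumptions), the variances are 0.84 + 1 − 1.60 = 0.24 and 0.84 − 0.64 = 0.20. The ratio is 0.83, and power is about 95% against 97%. Covariates entered only as between-subject main effects would not sharpen the Group-by-Follow-ups test at all.

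**Conclusion.** The point holds as a modest loss of efficiency in a valid, conservative analysis. At the article's correlation of 0.80, the unadjusted change-score comparison at T1 has about 11% more variance than a baseline-adjusted one (0.40 against 0.36). This is worth about four points of power at a 0.43 SD difference. That difference is an assumption, chosen as roughly what 34 per arm can detect with 80% power. At an assumed correlation of 0.5 the variance ratio falls to 0.75 and the power gain is about 11 points.

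The 3.9% size depends on EDRC being the balanced score and on perfect balance. The simulated figures depend on tuning values that the article does not state. The benefit of adding age and BMI cannot be quantified from the document, because it gives no relation of either to EDRC; the case for including them is that allocation was balanced on them.

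**What to change.** In Statistical methods, analyse post-baseline EDRC at T1 to T5 (or the changes) with these covariates: baseline EDRC, the EDI-3 severity score used for balancing if it is a different one, age and baseline BMI. Let the baseline EDRC effect vary by visit, so that the adjustment reaches the visit-specific comparison, and name the T1 group difference as the primary contrast. T0 is then a covariate and not a level of the within-factor. In Allocation, state which EDI-3 score is balanced.

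Adjust each secondary psychological outcome, and BMI, for its own baseline value.

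The cost is a few sentences and a few degrees of freedom. All the variables are already collected at T0. The change should be recorded before unblinding.

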### Blinding

The investigators, the highly trained ED professionals involved in the TAU and participants, as well as their parents, will be blinded to the group allocation. In addition, data for each measure will be collected from blinded experimenters and will be insert in electronic and protected data files.

Randomization information will be maintained until data collection is completed by an independent researcher, who will have an emergency code break envelope to open in case of serious adverse event that requires knowledge of the interventions to manage the participant’s condition.

### Safety considerations

The risks associated with participation in the study are low. One possible critical aspect is related to the use of NIBS itself. Standard NIBS paradigms are considered safe and well-tolerated in developmental age [70] including those with underlying neurological conditions or mental disorders [71]. Safety guidelines for the application of TMS and tDCS in pediatric patients report no serious adverse events, but only mild and transient [34, 70, 72].

Previous studies conducted by our laboratory [40, 56–59, 73] have also demonstrated the safety and tolerability of tDCS and its usefulness in improving cognitive and psychopathological measures in children and adolescents with developmental and psychopathological disorders.

Adverse effects will be registered during the total time of the study, using a standard questionnaire [68, 69]. The experimenter will follow participants for adverse effects even after the end of the study.

### Study monitoring and data management

The principal investigator (or the ethics committee) will identify a study monitor assigned to follow this study in accordance with this Clinical Trial Protocol [European guidelines for Good Clinical Practice (CPMP/ICH/135/1995) and Decree-Law Italian Minister of Health, 15 July 1997]. The Investigator agrees to provide reliable data and all information requested by the Protocol (with the help of the Case Report Form (CRF), or other appropriate instruments) in an accurate and legible manner according to the instructions provided and to ensure direct access to source documents to the ethics committee representatives. If any particular circuits have to be defined (e.g., e-CRF, Fax), particular attention should be paid to the confidentiality of the patient’s data to be transferred.

The principal investigator may appoint such other individuals as he/she may deem appropriate as Sub-Investigators to assist in the conduct of the Clinical Trial in accordance with the Clinical Trial Protocol. All Sub-Investigators shall be timely appointed and listed. The Sub-Investigators will be supervised by and under the responsibility of the Investigator. The Investigator will provide them with a Clinical Trial Protocol and all necessary information.

The participants’ personal data will be anonymous and coded. The hard files will be placed in a closed drawer. The database will be protected by password. The investigators will allow the monitoring of the data at an appropriate frequency. The original documents will be available at any time to be verified by the clinical monitor and regulatory authority.

